Previous studies have established economic, socio-cultural and geographic barriers to care seeking for childhood illness in the developing world, including Nepal [1, 14–16]. Even in places where appropriate health services are available, they are not fully utilitised [17]. Community based interventions have been trialled to improve engagement with health services and decrease childhood morbidity and mortality [18–20]. The World Health Organisation has produced a primary ear care programme to educate and motivate the community about ear infections and the need to take action to prevent CSOM and hearing loss [21]. This programme is simple and can easily be adapted to cultural contexts and delivered in a socially acceptable setting. There have been few previous successful interventions aimed at prevention and early treatment of CSOM and no published data on the effectiveness of community education or primary ear care training for the community. Consequently, this trial tests the hypothesis that simple ear training can improve maternal practice and reduce the prevalence of the complications of acute ear infections.

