### Study design

Our study uses a cluster randomised trial design and is profoundly informed by our previous qualitative study (unpublished), consisting of in-depth interviews with women in Jumla, Nepal. Existing women’s self-help groups will be the unit of randomisation, or cluster. This is a suitable method for an intervention that takes place at the group level and is commonly used in community-based interventions [18, 19, 22–24]. Stratification will be done to avoid sampling bias, as power is better maintained than with matching. The 56 existing groups will be stratified into according to Village Development Committee and the remoteness of their location and distance to the road. Although all of these groups are in a remote location, distance to the road determines accessibility of health and other services. Following stratification, a random sample of 30 groups will be chosen for the study. Randomisation will be done using a computer generated random number sequence in Australia, by a member of the team (HW) not involved in data collection. The selection will then be communicated to the field team leader by internet or telephone. We will seek individual informed consent from each participant woman. After baseline data collection, groups will be randomly allocated to the intervention group and to the control group, stratified by geography. Randomisation will again be performed by a team member in Australia using a computer generated random number sequence and communicated to the field team leader by internet or telephone. The intervention will then be implemented over three consecutive regular monthly meetings of the self-help groups. International Nepal Fellowship is the only non-government organisation working directly with women in the two Village Development Committees, so it is unlikely that any co-interventions might contaminate the study. Women in Jumla are not generally mobile. A small number of women do migrate to India to work with their husbands and these women could be lost to follow-up but the numbers are likely to be very small. In the 2011 census, only 341 women in the entire district of Jumla were absent from their their homes [25]. Follow-up assessment at 12 months, repeating the women’s questionnaire and examination of the children’s ears will complete the study. Ethical approval has been granted by Human Research Ethics Committee, University of New South Wales (Ref# 13361) and Nepal Health Research Council (Ref # 1434).

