
#### Secondary outcome measure—examination of the children’s ears

The other part of the baseline data collection is examination of the children’s ears. The secondary outcome measure is a reduction in the prevalence of CSOM and other abnormalities of the tympanic membrane in the intervention group compared to the control group. We will also offer a health check to all of the children. It is likely that this will be well-received as it is rare for a medical doctor to leave the district capital. The field team leader, an experienced Australian General Practitioner, will examine the children’s ears and take a digital image of their eardrums with a Welch Allyn Digital Macroview Otoscope, if possible, for later verification with an Ear Nose and Throat specialist blinded to allocation. All images will be identified by number only and submitted to the Ear Nose and Throat specialist who will be the final arbiter of diagnosis. CSOM will be diagnosed according to WHO Guidelines with aural discharge of more than two weeks [1]. There is considerable variation internationally about the duration of discharge needed to diagnose CSOM, so children with discharge for longer than six weeks and three months will be documented and analysed separately [38]. Height, weight, middle upper arm circumference, vision, heart and skin checks will also be performed. Weight will be measured to nearest 100 g with Seca 876 scales, height will be measured to nearest 1 mm with Seca 217 mobile height measurement and length to nearest 1 mm with Seca 210 mobile measurement mat. Vision checks will use Revised Sheridan Gardiner Test, which is suitable for illiterate children. Research assistants will be trained in accurate use of equipment and recording of data by the field team leader using WHO Training Course on Child Growth Assessment (2008) [39]. The field team leader will perform skin, heart and ear examinations. Children with medical issues will be referred to health posts or the local hospital, as appropriate. Any child with a current ear infection will also be offered treatment or referral to local health services. There is no specialist ear service in Jumla It would not be ethical to deny treatment to any child. Results of the examination will be recorded on a paper that will also record the ID number of their mother or grandmother**.**

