
### Statistical analysis

Analysis will be by intention-to-treat, all study participants will be included in the analysis, even if lost to follow-up. Analysis will be adjusted for clustering. Every effort will be made to have complete data but missing data will not be ignored in the analysis. Data will be checked and cleaned before being entered into Statistical Package for the Social Sciences. At baseline a comparison profile of both intervention and control groups will be provided. The primary and secondary outcomes - difference in mean questionnaire score and prevalence of CSOM - will be compared between the two groups. Data will be analysed at both individual and cluster level. Cluster level analysis is very robust and, with 15 clusters in each arm, individual level analysis, adjusted for clustering ought also to be very robust. For the primary outcome, a summary measure, the mean score of the questionnaire, will be calculated and then the intervention and control group compared for significance with a *t*-test at the cluster level. For individual level analysis, we plan to use mixed effects linear regression, which adjusts for the effect of clustering. The secondary outcome is a proportion, so we plan to analyse individual level data using logistic regression random effects model, using quadrature checks, which also adjusts for clustering. Since the age range is quite broad we will consider each standard age grouping in our analysis: under one year, under five years, and five years and over. We will also analyse duration of ear discharge as this is strongly correlated with prognosis. Covariates including socioeconomic status, education, caste, geography and number of household members will be considered.

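### The analysis of CSOM at 12 months does not name baseline ear status as a covariate, although ears are examined before allocation; pooled prevalence may under- or overstate prevention

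*Protocol article*

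**What the plan says.** All references are to the protocol article; no separate SAP is at hand.

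- **Outcome** (Secondary outcome measure): "The secondary outcome measure is a reduction in the prevalence of CSOM and other abnormalities of the tympanic membrane in the intervention group" compared with control. The hypothesis in the Background is also about prevalence: "simple ear training can improve maternal practice and reduce the prevalence of the complications of acute ear infections".
- **Baseline measurement** (same section): "The other part of the baseline data collection is examination of the" children's ears. Allocation follows (Study design): "After baseline data collection, groups will be randomly allocated to the intervention group and to the control group, stratified by geography".
- **Who enters** (Inclusion and Exclusion criteria): children in participating households up to age 12. Existing ear disease is not an exclusion.
- **Care of cases found** (Secondary outcome measure): "Any child with a current ear infection will also be offered treatment or referral to local health services". At baseline this comes before allocation, so it applies to both arms.
- **Follow-up** (Study design): "Follow-up assessment at 12 months, repeating the" women's questionnaire and the ear examination.
- **Model** (Statistical analysis): "The secondary outcome is a proportion, so we plan to analyse individual level data using logistic regression random effects model".
- **Covariates** (same section): "Covariates including socioeconomic status, education, caste, geography and number of household members will be considered". Age groupings and duration of discharge will also be looked at. The stated use of baseline data is a descriptive profile of the two arms.

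**The concern.** The Study population section calls CSOM a chronic condition, so whether a child has it at baseline is likely to predict whether the child has it a year later. That value is collected, but the article does not commit to using it in the comparison. With 30 randomised units and an uncommon outcome, two things follow. The estimate is less precise than the data allow, and any chance difference in baseline CSOM between arms carries into the 12-month comparison to the extent that disease persists.

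There is also a question of interpretation. The Discussion presents the trial as an attempt to prevent CSOM. Prevalence at 12 months counts children who developed CSOM together with children who already had it. No stated analysis separates the two, so the prevalence result cannot be read directly as the size of a preventive effect.

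**Working it through.** **The plan's own figure.** The only sample size is for the questionnaire score: DEff = 1 + (20 − 1) × 0.05 = 1.95, and 114 × 1.95 = 222.3, rounded up to 223 women per arm. This reproduces. No size or power is stated for CSOM.

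**Inputs from the article.** 15 clusters per arm; about 600 women in total; CSOM prevalence p0 = 7.6% (Background, ages 5 to 13, so only a proxy for ages up to 12).

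**Assumptions, not in the article.** 600 children per arm (40 per cluster), except where 300 to 900 is shown; ICC for CSOM 0.01 to 0.05; share of baseline cases still affected at 12 months s = 0 to 80%; CSOM at 12 months among children free of it at baseline i = 2% to 4%.

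**1. Chance imbalance at baseline** (stratification ignored).
SE = √(2 × 0.076 × 0.924 / 600 × DEff), with DEff = 1 + 39 × ICC.

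| ICC | DEff | SE (points) | 1.96 × SE (points) |
|---|---|---|---|
| 0.01 | 1.39 | 1.80 | 3.5 |
| 0.03 | 2.17 | 2.25 | 4.4 |
| 0.05 | 2.95 | 2.63 | 5.2 |

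With no intervention effect, 12-month prevalence is i + p0(s − i). A baseline difference d therefore carries forward as d × (s − i). For d = 4.4 points:
- s = 10%, i = 4%: 4.4 × 0.06 = 0.3 points
- s = 25%, i = 4%: 4.4 × 0.21 = 0.9 points
- s = 80%, i = 2%: 4.4 × 0.78 = 3.4 points

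**2. Precision on offer.** The share of child-level variance in 12-month CSOM explained by baseline CSOM (clustering ignored) is p0(1 − p0)(s − i)² / [p(1 − p)], where p = p0·s + (1 − p0)·i.
- s = 10%, i = 4%: 0.0702 × 0.0036 / 0.0426 = 0.6%
- s = 25%, i = 4%: 0.0702 × 0.0441 / 0.0528 = 6%
- s = 80%, i = 2%: 0.0702 × 0.6084 / 0.0730 = 59%

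The gain is negligible if nearly all baseline cases resolve and large if most persist.

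**3. What pooled prevalence does to a preventive effect.**
Control: p0·s + (1 − p0)·i. Intervention: p0·s·RRp + (1 − p0)·i·RRi, where RRi acts on new and RRp on persisting disease.
Worked case, s = 25%, i = 4%, RRi = 0.5, RRp = 1: control 0.0190 + 0.0370 = 0.0560; intervention 0.0190 + 0.0185 = 0.0375; ratio 0.67.

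| Scenario | Prevalence ratio |
|---|---|
| RRi 0.5, RRp 1, s = 0 | 0.50 |
| RRi 0.5, RRp 1, s = 10% | 0.59–0.65 |
| RRi 0.5, RRp 1, s = 25% | 0.67–0.75 |
| RRi 0.5, RRp 1, s = 50% | 0.75–0.84 |
| RRi 0.5, RRp 1, s = 80% | 0.81–0.88 |
| RRi 0.5, RRp 0.5, any s | 0.50 |
| RRi 0.75, RRp 0.5, s = 10–80% | 0.56–0.71 |

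In the last row the prevalence ratio is stronger than the preventive effect of 0.75. One simple scenario lies inside this table: 46 cases (0.076 × 600), half persisting and half new. Halving new disease alone gives 23 + 11.5 = 34.5, a 25% fall in prevalence against a 50% fall in new disease.

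**4. Power** at s = 25%, i = 4%, RRi = 0.5, ICC 0.03. Power = Φ(difference / √[(p1q1 + p2q2)/n_eff] − 1.96), with n_eff = children / DEff.
- Prevalence, RRp = 1: n_eff = 600 / 2.17 = 276; 0.0185 / 0.0179 = 1.03; power about 18% (13% to 20% for 300 to 900 children per arm).
- New CSOM only, 4% against 2%: 600 × 0.924 = 554 children, about 37 per cluster, DEff 2.08, n_eff = 267; 0.0200 / 0.0147 = 1.36; power about 27% (20% to 31%).
- Prevalence, RRp = 0.5 (0.0560 against 0.0280): 0.0280 / 0.0170 = 1.65; power about 38%, above the new-disease analysis.

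**The case against.** Prevalence is what the article sets out to reduce, in its aim, hypothesis and outcome. Randomisation makes the 12-month comparison valid without any baseline term, and chance imbalance is already reflected in the standard error. All of that stands: this is a matter of efficiency and interpretation, not of bias or a wrong endpoint.

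A reader might infer that any preventive effect must be diluted. The article does not support this. Sessions 1 and 2 teach care-seeking, ear mopping and the giving of drops, and the Session 3 card illustrates the care of a discharging ear, so education may help existing cases too. Dilution then shrinks, vanishes or reverses (working, step 3). The offer of treatment or referral in both arms also cuts both ways: it narrows the contrast on existing cases, but leaves fewer of them to carry over.

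A reader might also infer that a null result would be uninterpretable. That goes too far. A null would be hard to read as evidence on prevention, but mostly because events are few and the trial was not sized for CSOM. Separating new disease lifts power only from about 18% to 27% in a favourable scenario.

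Nor can one say that baseline status will not be used. The covariate list is open, a fuller plan may exist, and age groupings are already foreseen. What remains is that the article names its model and covariates, omits a likely prognostic variable that it collects, and an open list commits the trial to nothing.

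Finally, about 46 baseline cases per arm is about 3 per cluster (46 / 15), too sparse for a stable random-effects model. Two snapshots a year apart also cannot tell persistence from resolution and relapse. Both points stand, and they limit the subset results to description.

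**Conclusion.** The concern holds in a limited form. The planned comparison of 12-month prevalence is valid, but it does not name baseline ear status, a collected and probably prognostic variable. If the 7.6% prevalence applies, with 600 children per arm and an ICC of 0.01 to 0.05, chance alone could separate the arms at baseline by about 3.5 to 5.2 points. How much of this reaches the 12-month estimate, and how much precision adjustment recovers, depends on persistence: under 1% of child-level variance if 10% of cases persist, and more than half if 80% persist and new disease is rare.

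As a measure of prevention alone, the prevalence ratio can be too weak (0.59 to 0.88 for a true halving), exact, or too strong. The direction depends on how many baseline cases persist and on whether education helps them, and the article gives neither. The 25% against 50% contrast is one assumed scenario, not an estimate of what will happen.

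**What to change.** Keep CSOM prevalence at 12 months as the secondary outcome and the random-effects logistic model as its analysis. Before follow-up data are analysed, pre-specify two covariates: baseline CSOM status and age. Use child-level status where available, or the cluster's baseline prevalence, so that children without a baseline examination are not dropped. Because adjustment in a logistic model changes the odds ratio being estimated, state which version is the main one and show the other beside it.

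Report two results as descriptive support only, by arm: new CSOM at 12 months among children free of it at baseline, and CSOM still present among those who had it. Do not attach confirmatory tests to them.

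The change needs no new measurement and no change to care. It costs some analysis wording and the linkage of each child's two examination forms. The forms carry numbers and the mother's or grandmother's ID, so it should be confirmed that an individual child can be matched across visits. The descriptive subsets will have few events, and the text should say so.

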## Discussion

This trial will be the first randomised controlled trial to try to establish the effectiveness of a community based intervention to improve the ear health of children in Nepal. We have designed an intervention that is consistent with community values, expectations and experiences, using local existing resources. We have postulated that asking women what they want to know, how they like to learn and what is important to them, formulating an intervention on those principles, and then delivering it in a familiar, acceptable setting will increase its uptake. We will direct women to seek help at existing health services – health posts and outpatient clinics. Health posts offer treatment and medication at no cost to the patient and, in Jumla, are readily accessible by foot. However, availability of care is not equivalent to access to care. Lack of knowledge, lack of threat perception, disempowerment, gender inequity all conspire together with poverty and geographical isolation to prevent adequate treatment of ear disease in children. Women’s groups have been a potent means of health education, empowerment and training in Nepal, improving maternal and child health. They are the ideal medium for a participatory, culturally contextual, engaging intervention to attempt to prevent CSOM.

## Trial status

Commenced data collection.

## Abbreviations

CSOM: Chronic suppurative otitis media
DEff: Design effect
ICC: Intracluster correlation coefficient
WHO: World Health Organisation
